**Fig. 2 Fig2:**
[figure not shown]
Schedule of enrolment, interventions and assessments

### Blinding

For the primary endpoint, Peak VO_2_, as the exercise physiologist supervises both the CPET test and the HIIT exercise program, he is not blinded. The Peak VO_2_ is measured at the point of maximal effort, which is reached with the encouragement of two independent researchers. In terms of secondary endpoints, the documentation of complications and administration of the questionnaires is performed by the principal investigator and a research assistant who are blinded to the group the patient has been randomised to. The study statistician will use non-informative study codes and remains blinded as to the actual allocation groups until all primary analyses are completed.

### Statistical analysis of sample size

As the literature, at the time of designing this study, did not provide the information needed to estimate the standard deviation for changes in Peak VO_2_ following 14 sessions of HIIT, it was decided to use an adaptive design, where the changes in peak VO_2_ in the exercise and control groups will be assessed after 30 patients have completed the study. At that stage, the required sample size to complete the study will be calculated using a group-blinded interim analysis where only the standard deviations will be calculated. No other statistical analyses will be performed before the conclusion of data collection. The only reason for stopping the study at this stage will be if sufficient participants have been recruited to meet the requirements of the sample size calculation.

### Statistical methods for analysis of endpoints

Patient demographics will be described using appropriate descriptive statistics (mean and standard deviation for normally distributed continuous variables, median and interquartile range for other continuous variables, count and percentage for categorical variables). The main statistical analyses will be directed at answering per-protocol questions around whether 14 (on a per-protocol basis we will accept ten or more) training sessions is efficacious at improving conditioning before surgery and at improving postoperative outcomes compared to no training sessions. Additional analyses will investigate all patients who were randomised in an intention-to-treat analysis (as allocated and using imputed data as needed). Differences in changes of Peak VO2 (the primary outcome) and SF-36 scores between the HIIT and usual care groups will each be separately modelled using linear regression with adjustment for baseline values (mixed for SF-36 with a random patient effect to accommodate the repeated outcome measurements at week 6 and month 3 and an interaction between group and time). The models will also adjust for age, surgery type and ASA score. Linear mixed models will similarly be used for the surgical recovery scores (day 5 and week 6) with a random patient effect, interaction between group and time, and adjusting for surgery type and ASA score. Linear regression will be used to compare length of stay (days) between groups adjusting for surgery type and ASA score. Usual model diagnostics will be used (including checking normality and homoscedasticity of residuals) and where necessary natural logarithmic transformation of dependent variables or quantile regression to model medians will be used. Differences between groups in postoperative complications (yes/no) and day 5 postoperative morbidity scale (0–9 and dichotomised) will be compared using Poisson regression with robust standard errors, providing estimated relative risks, adjusting for surgery type and ASA score. Missing data will be replaced using multiple imputation for both the per-protocol and intention-to-treat analyses with chained estimating equations. Statistical analyses will be performed using R 3.4.1 or Stata 15.0 and statistical significance will be determined by two-sided *p* < 0.05.

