## Background

While complications continue to be a common event after abdominal surgery [1], the ability to predict who will develop perioperative complications remains difficult because the aetiology of adverse events is multifactorial [2]. In terms of reducing the likelihood of complications, many of the most important risk factors—such as the number of pre-existing co-morbidities, the extent of the underlying pathology and the magnitude of the required operation—cannot be changed before surgery. Stopping smoking [3] and optimising specific medical problems will improve the outcome in some patients. However, one important risk factor which it may be possible to improve in a significant group of patients is the functional reserve or the cardiopulmonary fitness of the patient.

Cardiopulmonary fitness can be assessed by measuring oxygen consumption during cardiopulmonary exercise testing (CPET). We know that this is an important clinical measurement as a poor oxygen consumption, including an anaerobic threshold (AT) of < 10-11 mL/kg/min [4–6] or a peak oxygen consumption (Peak VO_2_) of < 15–18.6 mL/kg/min [7], has been demonstrated to be associated with significantly higher rates of postoperative complications. In general terms, a low oxygen consumption is also predictive of a higher medium-term mortality risk [8], and it has been estimated that approximately half of patients presenting for intra-abdominal surgery do not have the prerequisite fitness on objective exercise testing to be considered at low risk for postoperative complications [9].

The main types of aerobic exercise which may improve oxygen consumption are High Intensity Interval Training (HIIT) and continuous moderate exercise. General studies (not perioperative) comparing the impact of these different types of exercise have shown that HIIT results in a more substantial [10] and faster [11, 12] improvement in Peak VO_2_ than continuous moderate exercise. The faster improvement is important in the context of surgery, as the urgency of the required surgery may mean that there is a limited period of time available between the time of diagnosis and surgery. There is also some evidence that a supervised HIIT program is safe in patients with moderate coronary artery disease and cardiac failure [12].

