### Participant progress through the study

The study design is outlined in Fig. 1. In terms of patient care, all eligible participants have been assessed by their surgical team and by the hospital’s anaesthetic preassessment clinic. Potential participants for the study are identified when they are booked onto a list (with a specific date) for their operation. Those who are 4–6 weeks out from surgery, who live in or around Dunedin, and do not have any obvious exclusion criteria are contacted by the research nurse. Those who are interested are then invited to visit the hospital. Following discussion about the aims of the study and familiarisation with the study protocol, the participant is given written information about the study, is interviewed by the research nurse and is assessed by the study’s anaesthetist. When all questions are answered, and if there are no exclusion criteria, consent is obtained by the research nurse and the first cardiopulmonary exercise test (CPET) is performed. Baseline clinical data obtained before the CPET test includes full clinical history and examination, investigations done as part of the participant’s preoperative workup, up-to-date vital signs and a SF-36 quality of life score. The results of the CPET test are checked by a cardiologist and following this the participant is accepted into the study and randomly allocated 1:1 to standard care or to the exercise training group by the exercise physiologist. Randomisation was performed in blocks of unequal length (equal probabilities of 2, 4 and 6 lengths), using computerised sequence numbers generated in Stata, with no stratification. The allocation code is kept in sealed opaque envelopes which are sequentially opened. The allocation sequence was generated by the study statistician who has no involvement in the enrolment, assignment or assessment of participants. The enrolment of patients is coordinated by the research nurse. The number of patients approached, those excluded and those who declined to be involved (with reasons given for this) is also being documented as it the participant’s preference for exercise training or normal care.

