In terms of design of the study and statistical analysis, issues with respect to insufficient data to perform a sample size calculation were discussed under ‘statistical analysis of sample size’. A second issue is the potential impact of chance differences in operations between the two groups on our secondary endpoints. Previous studies reporting on the perioperative use of aerobic exercise have usually been for patients having the same operation (such as a liver resection [18], anterior resection [15] or aortic aneurysm repair [19]). This present study includes patients having a range of different abdominal operations, which are known to have different rates of postoperative complications. Although differences in operations are not expected to impact on our primary endpoint (changes in preoperative Peak VO_2_), these may impact on our secondary endpoints. We will therefore adjust for surgery type and ASA score when performing our statistical analysis. By reducing the unexplained variance in the data, this should improve the precision of our estimates of intervention effects while also correcting for imbalances that arise by chance.

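### Four postoperative models (length of stay, complications, POMS, surgical recovery) omit baseline Peak VO2, which the protocol cites as a predictor of complications and measures in everyone before randomisation

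*Protocol article*

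**What the plan says.** The section on statistical methods for endpoints fixes the covariates model by model.

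- **Change in Peak VO2, and SF-36 (week 6 and month 3):** each adjusts for its own baseline, and "The models will also adjust for age, surgery type and ASA score".
- **Surgical recovery score (day 5 and week 6):** a linear mixed model "with a random patient effect, interaction between group and time, and adjusting for surgery type and ASA score".
- **Length of stay:** "Linear regression will be used to compare length of stay (days) between groups adjusting for surgery type and ASA score".
- **Complications and day 5 POMS:** "Poisson regression with robust standard errors, providing estimated relative risks, adjusting for surgery type and ASA score".

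The Background says that a low anaerobic threshold or a Peak VO2 below 15-18.6 mL/kg/min "has been demonstrated to be associated with significantly higher rates of postoperative complications". Allocation was made "using computerised sequence numbers generated in Stata, with no stratification". The Discussion, under challenges in running the trial, explains the choice of surgery type and ASA: operations differ in their complication rates, and "By reducing the unexplained variance in the data, this should improve the precision of our estimates of intervention effects", while chance imbalances are also corrected.

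**The concern.** The protocol gives two purposes for adjustment, precision and correction of chance imbalance. Baseline Peak VO2 serves both. It is the patient characteristic on which the trial's rationale rests, and it is already collected. These four outcomes have no preoperative value of their own to adjust for, unlike SF-36, so baseline fitness is the nearest thing to a baseline measure that they have. The article explains why operation type is included but not why fitness is left out, or why age enters the SF-36 model and not these four, when eligible ages run from 45 to 85.

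At stake is some precision on endpoints that are unpowered to begin with. In the per-protocol analysis there is also the risk that a difference in starting fitness between the retained groups is read as an effect of training, or hides one.

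**Working it through.** The article states no final sample size, standard deviation or event rate for these outcomes, so there is no figure of the plan's to reproduce. Every input below that is not a covariate list is an assumption.

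**1. Is baseline Peak VO2 a true baseline covariate?** The sections on participant progress and on interventions place the first exercise test before randomisation, and a contraindication found on it stops randomisation. The Outcomes section describes the value as documented after randomisation. That sentence needs correcting, but the sequence of events is clear from the other two sections.

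**2. Chance imbalance.** For a standardised covariate under unstratified 1:1 allocation of N patients in total, the SD of the between-arm difference is √(4/N).

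| N | SD of imbalance | P(imbalance beyond 0.5 SD) |
|---|---|---|
| 30 | 0.37 | 17% |
| 60 | 0.26 | 5% |
| 100 | 0.20 | 1% |

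**3. Precision, linear outcomes.** Adding one covariate that explains a further share R² of the outcome variance, beyond surgery type and ASA, multiplies the variance of the treatment contrast by about (1 − R²) × (1 + 1/(N − 8)). This assumes six other parameters besides the intercept. Correlations of 0.3 and 0.4 give R² = 0.09 and 0.16; 0.20 is an upper case.

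| R² | N = 30 | N = 60 | N = 100 |
|---|---|---|---|
| 0.09 | 0.91 × 1.045 = 0.951, SE −2.5% | 0.91 × 1.019 = 0.928, SE −3.7% | 0.91 × 1.011 = 0.920, SE −4.1% |
| 0.16 | 0.84 × 1.045 = 0.878, SE −6.3% | 0.84 × 1.019 = 0.856, SE −7.5% | 0.84 × 1.011 = 0.849, SE −7.9% |
| 0.20 | 0.80 × 1.045 = 0.836, SE −8.5% | 0.80 × 1.019 = 0.815, SE −9.7% | 0.80 × 1.011 = 0.809, SE −10.1% |

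Simulation on assumed inputs gave about 3-11% for N = 30-100, in line with this. If the added R² is tiny the gain disappears: with Peak VO2 and age together and R² = 0.02, the SE rises by 3.6% at N = 30 and 0.9% at N = 60.

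**4. Precision, Poisson relative risks.** The linear formula does not carry over. In simulation, Peak VO2 alone raised the SE of the log relative risk by about 3-4% at N = 30 and was about neutral to 4% better from N = 50. Peak VO2 and age together did worse: +12% to +15% at N = 30, 0% to +3.5% at N = 50, and −3% to +1% at N = 100. The two-covariate figures assume about 40% complications, three surgery classes, binary ASA, and a relative risk of 0.7-0.8 per SD of fitness.

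**5. Per-protocol set.** The main analyses, including those of postoperative outcomes, keep HIIT patients with ten or more sessions and drop controls who report substantial higher-intensity exercise. Suppose 70-80% adherence, with the log-odds of adhering rising by 0.5-1.0 per SD of fitness. The retained HIIT arm is then 0.10-0.25 SD fitter. At a complication relative risk of 0.7-0.8 per SD and no treatment effect, the spurious relative risk runs from 0.8^0.10 = 0.98 to 0.7^0.25 = 0.91. If 20-30% of controls are also excluded, with the same slope towards the fitter ones, the gap is 0.19-0.50 SD and the spurious relative risk runs from 0.8^0.19 = 0.96 to 0.7^0.50 = 0.84.

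**The case against.** The strongest reply is that this is a preference. A short, prespecified covariate set with a stated reason is defensible for secondary endpoints that the article itself calls unpowered. Citing a predictor does not commit a plan to adjusting for it. The Background association is a threshold association with complications; it is not shown to hold within surgery type and ASA, and that section does not report it for length of stay, POMS or recovery. All of this stands, and it limits the point to a recommended improvement.

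A reader might infer several stronger things that the document does not support.

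- **That no postoperative model goes beyond surgery type and ASA.** The SF-36 model is postoperative and also has its own baseline and age.
- **That unstratified allocation biases these estimates.** In the intention-to-treat comparison, chance imbalance in an omitted covariate is already counted in the standard error. Mean differences and relative risks are collapsible, so the cost there is precision.
- **That the next trial would be wrongly sized.** The article plans to size it from the distribution of the chosen endpoint, which does not depend on the covariates used in this trial's treatment contrast.
- **That surgery type should be collapsed to pay for the extra term.** The article does not say how many categories surgery type has.

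The per-protocol argument also has limits. The Discussion describes some enrolled patients who had been inactive, and some controls who then took up exercise of their own. If the excluded controls were the less fit ones, their exclusion would partly offset selection in the HIIT arm.

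**Conclusion.** The point holds in a modest form. Four models leave out a baseline variable that the protocol's own rationale singles out, that every randomised participant has, and that serves both stated purposes of adjustment. On assumed inputs the gain is an SE about 3-11% lower for length of stay and surgical recovery. For complications and POMS there is little or no gain, and a loss of a few percent if the final sample is near 30.

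The better reason to act is the per-protocol set. There the exclusions follow different rules in the two arms and plausibly relate to fitness, so baseline Peak VO2 may be a confounder that ASA captures only coarsely. The possible distortion, a relative risk of about 0.98 to 0.84 under no effect, rests wholly on assumed adherence, exclusion and prognostic strength, and its direction is not certain. Adjustment would reduce it but cannot guarantee its removal.

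**What to change.** Before unblinding, prespecify baseline Peak VO2 (mL/kg/min, one linear term) in the length of stay, complications, POMS and surgical recovery models, alongside surgery type and ASA, for both the per-protocol and the intention-to-treat analyses. Otherwise, give the reason for leaving it out.

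Age may be added for consistency with the Peak VO2 and SF-36 models, but it is optional: it adds little, and in the Poisson models the second term is expensive in a small sample. Once the interim review has set the sample size, and before outcomes are seen by arm, confirm whether the Poisson models can carry the extra term.

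The cost is a change of wording and one degree of freedom per model, or two with age. No new data are needed. The Outcomes sentence on when the first Peak VO2 is documented should be brought into line with the other two sections.

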**Methods:**

Consecutive eligible patients undergoing elective abdominal surgery are being randomised to HIIT or standard care in a 1:1 ratio. Participants allocated to HIIT will perform 14 exercise sessions on a stationary cycle ergometer, over a period of 4–6 weeks before surgery. The sessions, which are individualised, aim to start with ten repeated 1-min blocks of intense exercise with a target of reaching a heart rate exceeding 90% of the age predicted maximum, followed by 1 min of lower intensity cycling. As endurance improves, the duration of exercise is increased to achieve five 2-min intervals of high intensity exercise followed by 2 min of lower intensity cycling. Each training session lasts approximately 30 min. The primary endpoint, change in peak oxygen consumption (Peak VO_2_) measured during cardiopulmonary exercise testing, is assessed at baseline and before surgery. Secondary endpoints include postoperative complications, length of hospital stay and three clinically validated scores: the surgical recovery scale; the postoperative morbidity survey; and the SF-36 quality of life score. The standard deviation for changes in Peak VO_2_ will be assessed after the first 30 patients and will be used to calculate the required sample size.

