### Recruitment to the study

The study is being performed at Dunedin Public Hospital, which is a tertiary care university hospital servicing a large geographical area in the south of New Zealand.

All patients we identify as fulfilling the inclusion criteria are being invited to participate in the study.

The inclusion criteria are:patient requiring major abdominal surgery;aged 45–85 years;able to attend multiple supervised exercise sessions at the hospital;available during a 4–6-week window up to the time of the confirmed surgery.

The definition of major abdominal surgery is any abdominal procedure expected to last 2 h or with an anticipated blood loss > 500 mL [28]. This included all gastrointestinal resections, liver surgery, large abdominal wall hernia repairs, abdominal aortic aneurysm repair, hysterectomy, radical prostatectomy and nephrectomy. For the purposes of this study, procedures such as laparoscopic cholecystectomy or transurethral resection of the prostate are not considered to be major abdominal surgery.

The exclusion criteria are related to medical risk factors and to conditions or treatments which could independently alter the Peak VO_2_ in the weeks before surgery. These include:inability to exercise or to perform a CPET;contraindication to exercise found on CPET;uncontrolled hypertension (blood pressure > 180/100);experiencing clinical angina (this does not include patients with a history of ischaemic heart disease who have no symptomatic angina on appropriate medical treatment or those who have previously had a successful revascularisation procedure);myocardial infarction in the past three months;uncontrolled cardiac arrhythmias;aortic aneurysm > 6.5 cm;severe obstructive pulmonary disease with a FEV1 < 1.0 L;inability to provide consent;significant anaemia defined as a haemoglobin level < 80 g/L or being on a treatment which would increase the haemoglobin in the 4–6 weeks before surgery;preoperative chemotherapy during the 4–6 weeks before surgery; orshort course preoperative radiotherapy.

Protocol amendment number 01 was introduced in 19 April 2016 and increased the acceptable range for the age and the blood pressure of participants in the study to the levels listed above.

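### If the robust Poisson tests use an uncorrected standard error with a normal reference, the day 5 POMS count is tested at about 9–15% rather than 5% near 30 patients; the yes/no outcomes are much less affected

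*Protocol article*

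**What the plan says.** The Protocol article, under Statistical methods for analysis of endpoints, gives one method for three outcomes: complications (yes/no), the day 5 POMS score from 0 to 9, and the same score dichotomised. They "will be compared using Poisson regression with robust standard errors, providing estimated relative risks, adjusting for surgery type and ASA score". The same section says that "statistical significance will be determined by two-sided" p < 0.05, and does not exempt these outcomes. It does not say which robust estimator is meant, whether a small-sample correction applies, or how many levels surgery type and ASA have.

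Under Statistical analysis of sample size, the trial is sized from blinded standard deviations: changes in peak VO2 "will be assessed after 30 patients have completed the study". Ending at 30 is possible but conditional on the recalculated number already being met: "The only reason for stopping the study at this stage will be if sufficient participants have been recruited to meet the requirements of the sample" […].

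Under Recruitment to the study, the definition of major abdominal surgery names seven procedure groups: "This included all gastrointestinal resections, liver surgery, large abdominal wall hernia repairs, abdominal aortic aneurysm repair, hysterectomy, radical prostatectomy and nephrectomy". The Outcomes section says the study is not powered for the secondary endpoints and that they should inform later studies.

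**The concern.** The robust (sandwich) variance is built from squared residuals. A fitted model pulls its residuals towards zero, most strongly for patients in small covariate cells, so without correction the variance is too small when there are many terms for few patients. A normal reference adds to this. A skewed 0–9 count makes it worse, because a few high scores carry much of the information.

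The result would be intervals that are too narrow and chance differences in morbidity called significant. These endpoints are secondary, but the Background says the results will guide the choice of endpoint for the next trial. A falsely precise POMS result could steer that choice.

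There is also a labelling error that needs no simulation. A Poisson model of a 0–9 score estimates a ratio of mean scores, whereas the sentence says relative risks for all three outcomes.

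**Working it through.** The plan gives no sample size, power or standard deviation to reproduce. The only stated figure to test is the 5% two-sided level.

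**Step 1: when would 30 patients be enough?** The difference of 2 mL/kg/min is from the protocol; power is assumed. The number per arm is 2(z₁ + z₂)²SD²/2², rounded up. At 80% power, (1.96 + 0.84)² ≈ 7.85:
- SD 1.9: 2 × 7.85 × 3.61/4 = 14.2, so 15 per arm, 30 in total.
- SD 2.0: 32. SD 2.5: 50. SD 3.0: 72.

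At 90% power, SD 1.7 already needs 32. So ending at 30 requires an SD of about 1.9 or less (80%) or below 1.7 (90%).

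**Step 2: rough size of the effect.** With three ASA levels, the model has 1 + 1 + 2 + 2 = 6 coefficients for three surgery types and 1 + 1 + 6 + 2 = 10 for seven. Average leverage is k/N, and an uncorrected standard error is too small by roughly √(1 − k/N). The effective critical value is then 1.96 × √(1 − k/N).
- N = 30, k = 6: 1.96 × √0.80 = 1.75, a two-sided error of about 8%.
- N = 30, k = 10: 1.96 × √0.667 = 1.60, about 11%.
- N = 72: about 6% (k = 6) and 7% (k = 10).

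This ignores skewness (which raises the error for counts) and discreteness (which lowers it for yes/no outcomes).

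**Step 3: simulation under no group effect.** There were 3,000 data sets per setting, with 1:1 allocation and a Poisson log-link model on group, surgery type and ASA. The sandwich carried only the factor N/(N − 1) and was compared with 1.96.

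Assumed, because the document does not give them:
- Three surgery types (50/30/20%) or seven (40/15/12/10/8/8/7%), and three ASA levels (15/50/35%).
- Base POMS mean 1 or 2, either Poisson capped at 9 or beta-binomial over nine domains.
- Base complication rate 30%, 50% or 62%. The outer values reflect the 62% and 31% that the Background cites from another study.

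Monte Carlo standard error is √(0.05 × 0.95/3000) = 0.4 points at a true rate of 5%, and 0.5 points at 10%.

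| N | POMS 0–9, three types | POMS 0–9, seven types | Yes/no, three types | Yes/no, seven types |
|---|---|---|---|---|
| 30 | 8.9–11.6% | 11.6–14.8% | 4.8–6.2% | 7.5–9.9% |
| 40 | 7.9–9.9% | 9.5–12.2% | 5.0–5.9% | 5.7–7.0% |
| 50 | 7.1–8.4% | 8.5–10.8% | 4.9–5.6% | 5.7–6.4% |
| 72 | 6.0–8.2% | 7.4–8.6% | 4.6–5.2% | 5.8–6.4% |

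With two surgery types and two ASA levels, the yes/no error at 30 is 3.3–4.7%. Dichotomised POMS was not simulated separately and is taken to behave like the other yes/no outcome.

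**Step 4: corrected standard errors at N = 30, with t on N − k degrees of freedom.**
- HC2: POMS count 4.7–6.8%, yes/no 2.1–5.1%.
- HC3: POMS count 1.5–3.8%, yes/no 0.5–4.1%.

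**Step 5: fewer patients analysed.** The main analysis is per-protocol, so fewer than the recruited number may be analysed. At 24, the uncorrected error is 9.9–18.3% for the POMS count and 6.3–17.1% for yes/no outcomes. With seven types and a 30% base rate, HC2 with t still gives 13.5% for the yes/no outcome; with three types it gives 3.7%. The smallest of seven types then averages 0.07 × 24 = 1.7 patients, so the correction works only if sparse types are pooled.

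**The case against.** The strongest reply is that the protocol does not fix the estimator criticised here. It says only robust standard errors; a corrected version such as HC2 or HC3 is itself robust, and an article may leave that detail to the analysis plan. This stands, and it makes the finding conditional. It does not remove the labelling error, and it leaves a test that can miss its stated level unless the correction is specified.

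Three stronger readings are tempting, and the document does not support them:
- A reader might infer that all three outcomes are tested at 1.5 to 3 times the stated level. At 30 patients that range describes the POMS count only (8.9/5 = 1.8 to 14.8/5 = 3.0). The yes/no outcomes are close to 5% with three surgery types and reach 1.5 to 2 times only with seven.
- A reader might take 30 as the final size. It is the point of the blinded review, and stopping there needs a small standard deviation. The excess for the POMS count does persist at 40 to 72, at a lower level.
- A reader might take the seven procedure groups as the model's categories. They illustrate eligibility; the coding of surgery type is not stated.

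It is also fair to say that these endpoints are secondary and declared unpowered, and that the primary analysis uses linear regression, which this point does not touch. That limits the consequence. It does not justify a test that misses its own stated level when the remedy is nearly free.

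**Conclusion.** The point holds conditionally, and mainly for the POMS 0–9 count. With an uncorrected sandwich and a normal reference, its actual two-sided error is about 9–15% at 30 patients, 7–11% at 50 and 6–9% at 72. For complications and dichotomised POMS the excess is small unless surgery type has many levels and the trial ends near 30.

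These figures rest on assumed POMS distributions, event rates and category frequencies. Multiple imputation and the per-protocol selection itself were not simulated. The mislabelling of the POMS 0–9 ratio holds without any of these assumptions. The conclusion on peak VO2 is not affected.

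**What to change.** - Keep the Poisson models and their point estimates.
- State that p-values and confidence intervals both come from one small-sample-corrected robust standard error, for example HC2 with t on residual degrees of freedom. HC3 with t is clearly conservative at 30.
- Define the surgery-type categories and pool sparse ones before unblinding.
- Report the POMS 0–9 result as a ratio of mean scores, and keep relative risk for the yes/no outcomes.

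A re-randomisation test is a less suitable main remedy. Per-protocol exclusions made after randomisation weaken its justification, imputation complicates it, and its p-values could disagree with intervals from a different method.

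The cost is about two sentences in the analysis plan and a few lines of code. Intervals become slightly wider, and the yes/no tests are somewhat conservative at about 30 patients (2–5%).
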